ASAS, Assessment of SpondyloArthritis International Society; axSpA, axial spondyloarthritis; BASDAI, Bath Ankylosing Spondylitis Disease Activity Index; CRP, C-reactive protein; DMARD, disease-modifying antirheumatic drug; HIV, human immunodeficiency virus; MRI, magnetic resonance imaging; NRS, numerical rating scale; NSAID, non-steroidal anti-inflammatory drug; SIJ, sacroiliac joint.

The study will include a 6-week screening period, a 16-week treatment period, and a safety follow-up at week 20. During the screening period, patients will be assessed for study eligibility and will undergo procedures outlined in the assessment schedule (Table 2). The baseline MRI of the SIJ will be performed within this period to assess the presence of active inflammation (bone marrow edema/osteitis) compatible with axial SpA (as assessed by two independent central readers, and an additional independent reader in case of disagreement) according to ASAS definition for positive MRI (“active sacroiliitis”).^
27
^ At baseline, eligible patients will be randomized on a 1:1 ratio by r-axSpA/nr-axSpA and elevated CRP/non-elevated CRP strata to receive either tofacitinib 5 mg two times daily (BID) plus naproxen 500 mg BID or matching tofacitinib placebo plus naproxen 500 mg BID for a 16-week double-blind treatment period (Figure 1). After the baseline visit, face-to-face clinical assessment will take place at weeks 4 and 16. An evaluation for early treatment response will be performed at week 4. Patients who maintain high disease activity according to BASDAI ⩾4 and demonstrate <20% improvement in BASDAI from baseline at week 4 will receive tofacitinib 5 mg BID open-label until week 16. After the last tofacitinib dose at week 16 or in case of early termination (only in patients who remained on treatment for at least 4 weeks during the study), primary, key secondary, and other efficacy secondary endpoints will be assessed. MRI of the SIJ will be performed in a maximum time window of ±7 days from the last visit.

**Table 2. table2-1759720X251324429:** Study procedures and timelines of the FASTLANE study.

Study procedures	Screening ⩽6 weeks	Baseline week 0	Week 4^ a ^	Week 16^ a ^/ET^ b ^	Week 20^ a ^/FU
	Visit 1	Visit 2	Visit 3	Visit 4	Visit 5 (phone)
Informed consent	X				
Inclusion/exclusion criteria	X	X^ c ^			
Randomization		X			
Demographics	X				
Medical/surgical history including VTE and cardiovascular risk assessment (SCORE2)	X	X^ c ^	X	X	
Contraception check^ d ^	X	X	X	X	X

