### Endpoints

The primary endpoint is the proportion of patients achieving an Axial Spondyloarthritis Disease Activity Score^
29
^ with CRP (ASDAS) <1.3 at week 16.

The key secondary endpoint is the change from baseline in the MRI SIJ SPARCC osteitis score at week 16. Other efficacy secondary endpoints are the proportion of patients achieving (1) ASDAS low disease activity (<2.1) at weeks 4 and 16; (2) ASDAS clinically important improvement (⩾1.1) at weeks 4 and 16; (3) ASDAS major improvement (⩾2.0) at weeks 4 and 16; (4) ASAS20 and ASAS40 response and ASAS partial remission at weeks 4 and 16; (5) BASDAI50 at weeks 4 and 16; (6) change from baseline in ASDAS, Physician Global Assessment, and serum CRP at weeks 4 and 16; and (7) change from baseline in BASDAI and PtGA at weeks 1, 2, 3, 4, 8, 12, and 16. In addition, the efficacy of tofacitinib 5 mg BID versus placebo on achieving early treatment response will be assessed by the proportion of subjects requiring treatment escalation to open-label tofacitinib at week 4. Additional secondary endpoints will include treatment responses on pain reduction (including very early response assessed daily within the first week of treatment), function, mobility, peripheral musculoskeletal manifestations, fatigue, quality of life, and extra-musculoskeletal manifestations at week 16 and at all other applicable time points. Safety secondary endpoints include incidence of adverse events (AEs), AE of special interest, and AEs leading to study discontinuation. Exploratory endpoints are the development of structural changes in the MRI of SIJ by the change from baseline in the SPARCC structural score of the MRI SIJs at week 16, and to assess the efficacy of tofacitinib 5 mg BID versus placebo by subgroup populations. The full list of study endpoints is found in Table 3.

**Table 3. table3-1759720X251324429:** Primary, secondary, and exploratory endpoints of the FASTLANE study.

*Primary endpoint*
Proportion of subjects achieving ASDAS <1.3 at week 16.
*Key secondary endpoint*
Change from baseline in the MRI SIJ SPARCC osteitis score at week 16.
*Other secondary endpoints*

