### Statistical analysis

The unblinded analysis will be performed on all patient data after the last patient has completed week 20 (or the last visit in early termination) and after the study database is locked.

Efficacy analyses will be performed in the modified intent-to-treat population that will be defined as all patients who are randomly assigned to study intervention with the investigational medicinal product (IMP, i.e., tofacitinib or placebo) and who have taken at least one dose of IMP. Participants will be analyzed using the treatment groups as they are randomized.

The primary analysis will focus on the proportion of patients who achieve remission, as defined by ASDAS <1.3 at the end of week 16. For comparison of tofacitinib versus placebo, the Mehrotra and Railkar^
31
^ method will be used, adjusting for the stratification factors (nr-axSpA/r-axSpA and elevated CRP/non-elevated CRP) if sufficient subjects are present in each stratum. Otherwise, the exact Chan and Zhang^
32
^ method will be applied. The difference in the remission rates between treatment groups and the corresponding two-sided 95% confidence interval adjusted for stratification factors will be reported. Missing values from patients who drop out or receive prohibited medication or treatment escalation for any reason before week 16 will be imputed as non-responders. For sensitivity analysis, the above analysis will be repeated using data as observed without missing imputation.

For the key secondary endpoint, change from baseline in MRI SIJ SPARCC osteitis score at week 16 will be analyzed using analysis of covariance adjusting for baseline score and stratification factor (if there are a sufficient number of subjects in each stratum, otherwise stratification factor will be removed from the model) to estimate the effect of initially randomized treatment. The least-squares means and the difference in least-squares means between treatment groups, both with their corresponding 95% confidence intervals will be presented. Data after patients receiving prohibited medicine or treatment escalation will be excluded from the analysis and only observed data will be used (missing data will not be imputed).

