For continuous secondary endpoints measured at a single visit, the same analysis as defined in the key secondary endpoint analysis will be repeated. For endpoints with multiple visits, change from baseline over time will be analyzed using the mixed-effect model for repeated measures accounting for fixed effects of baseline score, visit, treatment, treatment-by-visit interaction, and stratification factors (if sufficient patients in each stratum). For sensitivity analysis of key secondary endpoints and secondary continuous endpoints, missing data will be imputed using baseline observation carried forward and the above corresponding analysis will be repeated.

For binary secondary endpoints, the same analysis as defined in primary analysis and corresponding sensitivity analysis will be applied accordingly. Safety analyses will include all patients randomly assigned to study intervention and who take at least one dose of IMP. Participants will be analyzed according to the treatment they have actually received. AEs will be coded using the Medical Dictionary for Regulatory Activities. Safety data will be presented in tabular and/or graphical format and summarized descriptively, where appropriate.

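### The key secondary MRI analysis drops every patient escalated at week 4, so it does not estimate the randomised effect that it names

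*Protocol article*

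**What the plan says.** All references are to the protocol article.

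- **Endpoint (Endpoints).** "The key secondary endpoint is the change from baseline in the MRI SIJ SPARCC osteitis score at week 16".
- **MRI timing (Study population and design; Table 2).** The baseline scan belongs to screening: "The baseline MRI of the SIJ will be performed within this period". Table 2 marks one further scan, at week 16 or early termination, and none at week 4.
- **Escalation (Study population and design).** Patients in either arm whose BASDAI is still at least 4 at week 4 and who "demonstrate <20% improvement in BASDAI from baseline at week 4 will receive tofacitinib 5 mg BID open-label until week 16".
- **Key secondary analysis (Statistical analysis).** An ANCOVA adjusts for baseline score and, if numbers allow, the stratification factor. Its purpose is given as "to estimate the effect of initially randomized treatment". On post-escalation data: "Data after patients receiving prohibited medicine or treatment escalation will be excluded from the analysis and only observed data will be used", with the addition that "missing data will not be imputed".
- **Sensitivity analysis (Statistical analysis).** For this endpoint, "missing data will be imputed using baseline observation carried forward" (BOCF).
- **Contrast.** The primary endpoint keeps escalated patients, as non-responders. The proportion escalated at week 4 is itself listed as an efficacy endpoint.

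**The concern.** The exclusion rule and the MRI schedule look harmless separately. Together they remove the whole MRI outcome of every escalated patient. For endpoints with several visits, the repeated-measures model can still use values from before escalation; with a single follow-up scan there are none.

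Removal depends on week-4 BASDAI, which treatment can affect and which the ANCOVA does not include. The retained groups are then no longer the groups formed by randomisation. In the tofacitinib arm the rule also discards scans from patients who stay on 5 mg BID before and after week 4, although those scans show the effect of the assigned drug.

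At stake is the trial's only key secondary endpoint: possible bias in its treatment difference, and a loss of patients that the sample size did not allow for.

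**Working it through.** **1. The plan's own figure.** The sample size rests on the primary endpoint: 20% against 50% remission, 90% power, two-sided 0.05. With pooled variance, n per arm = [1.96·√(2·0.35·0.65) + 1.2816·√(0.2·0.8 + 0.5·0.5)]² / 0.3² = 51.01, rounded up to 52, so 104 in total. The figure reproduces. It says nothing about power for the MRI endpoint.

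**2. Who remains.** A patient escalated at week 4 has one scan before escalation (screening) and one after (week 16 or early termination). The second is excluded and not imputed, so no change score exists. This follows from the text and needs no assumption.

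**3. Inputs for size.** The documents give no escalation rates, MRI SD, MRI effect or correlation. The following are assumptions: true difference -4 SPARCC points; residual SD 6; escalation 30-50% on placebo and 15-20% on tofacitinib; correlation ρ of 0.2-0.5 within arm between week-4 improvement and week-16 MRI improvement.

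**4. Formula.** Suppose the share p with the least week-4 improvement is removed from an arm. The mean MRI improvement of those left then rises by ρ·SD·f(p), where f(p) = φ(z_p)/(1−p). The treatment difference shifts against tofacitinib by ρ·SD·[f(p_placebo) − f(p_tofacitinib)].

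Values: f(0.15) = 0.274, f(0.20) = 0.350, f(0.30) = 0.497, f(0.40) = 0.644, f(0.50) = 0.798.

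| Escalated, placebo / tofacitinib | ρ | Shift | Estimate (true -4) | Attenuation | Patients kept of 104 |
|---|---|---|---|---|---|
| any | 0 | 0 | -4.00 | 0% | – |
| 30% / 20% | 0.2 | 0.2·6·(0.497−0.350) = 0.18 | -3.82 | 4% | 78 |
| 40% / 15% | 0.3 | 0.3·6·(0.644−0.274) = 0.67 | -3.33 | 17% | 75 |
| 50% / 20% | 0.5 | 0.5·6·(0.798−0.350) = 1.34 | -2.66 | 34% | 68 |
| 50% / 15% | 0.5 | 0.5·6·(0.798−0.274) = 1.57 | -2.43 | 39% | 70 |

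A simulation of the ANCOVA as written (52 per arm, 3,000 trials, 40%/15%, ρ = 0.3) gave -3.30, in line with the third row. In this model equal escalation in the two arms also gives no shift.

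**5. No true MRI effect.** At 40%/15% the same shift gives +0.7 (ρ = 0.3) to +1.1 (ρ = 0.5) points against tofacitinib. The simulated standard error is 1.38.

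**6. Power from lost patients alone.** Power = Φ(d/√(1/n₀+1/n₁) − 1.96) with d = 0.65 SD:

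- all 52/52: 0.65/0.196 − 1.96 = 1.35, so 91%
- 30%/10% escalated (36.4 and 46.8 kept): 84%
- 40%/20% (31.2 and 41.6 kept): 78%
- 50%/20% (26 and 41.6 kept): 0.65/0.25 − 1.96 = 0.64, so 74%

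**7. BOCF.** If excluded values count as missing, every escalated patient is set to zero change. In the 40%/15%, ρ = 0.3 simulation this gave -3.34 with a model standard error of 1.07, below the 1.19 found when every patient is measured. BOCF also attenuates where the complete-case analysis does not: with 20% escalated in both arms and ρ = 0, it gives 0.8 × -4 = -3.2.

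**8. All observed scans by randomised arm.** If 40% of placebo patients take open-label tofacitinib and gain its full effect, the difference is -4 × (1 − 0.40) = -2.4 (simulated -2.38). This is a different quantity, the effect of assignment with escalation allowed, and not a biased version of -4.

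**The case against.** The strongest reply is that "to estimate the effect of initially randomized treatment" can mean the effect of the first-assigned treatment had nobody switched. Removing data after the switch fits that aim, so there is no contradiction in terms. That reading is fair, but it does not rescue the analysis. A complete-case ANCOVA then needs removal to be unrelated to MRI outcome given baseline score and strata, while removal is decided by week-4 BASDAI, which is not in the model.

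Other points stand and limit the finding:

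- A reader might infer that only week-4 responders are compared. Escalation needs both BASDAI of at least 4 and less than 20% improvement, so a patient below 4 with little improvement stays. Early terminators with at least four weeks of treatment may also contribute a scan.
- A reader might infer that more placebo patients will certainly be lost, or that a fixed share of scans goes. Both are plausible, but the documents give no rates.
- A reader might infer a risk of a false MRI claim for tofacitinib. In the scenarios above the bias runs the other way, and the shift under no effect is smaller than one standard error.
- BOCF does bring escalated patients back, much as the primary endpoint's non-responder rule does. It brackets part of the problem.
- Imputation is no free repair. Escalation is deterministic, so no escalated placebo patient has a week-16 scan without open-label tofacitinib, and any model extrapolates. In a large-sample check (40%/15%, truth -4), linear imputation was right when the relation was linear. It gave -4.9 when MRI change was flat among poor responders and -2.9 when flat among good responders; complete-case gave -3.5 in both.

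**Conclusion.** The point holds, at should-fix level. It is certain from the text that escalated patients leave the key secondary ANCOVA, and that the retained groups are selected on a post-randomisation efficacy outcome on which the model does not condition. The result therefore cannot be presented as the randomised effect in the modified intent-to-treat population.

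Bias needs two further conditions: week-4 response related to MRI change and, in the simple model used here, unequal escalation between arms. Given both, the most plausible direction is against tofacitinib. The 4-40% attenuation rests wholly on the assumed ranges; the documents fix neither size nor direction. The primary endpoint and the sample size of 104 are unaffected.

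**What to change.** 1. **Main analysis.** Analyse all observed week-16 MRIs by randomised arm regardless of escalation, with the same ANCOVA. This keeps the randomised comparison, is valid if the drug has no effect, and uses scans already scheduled. Its cost is dilution, because escalated placebo patients receive tofacitinib.
2. **If the effect without escalation is the intended target, say so.** Keep the tofacitinib-arm week-16 MRIs. Multiply impute escalated placebo patients with a model that includes treatment, baseline score, both stratification factors, and week-4 BASDAI, ASDAS and CRP. Because this extrapolates, add a delta-adjusted (tipping-point) sensitivity analysis.
3. **Complete-case and BOCF.** Keep both as supplementary only, and do not describe the complete-case result as the effect of the treatment initially randomised.

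The change costs protocol or analysis-plan wording and some programming, to be settled before unblinding. No new data are needed: Table 2 already schedules the week-4 clinical measures and the week-16 MRI.

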## Discussion

This trial addresses a relevant gap in the management of early axSpA, particularly in those patients with axial symptoms up to 2 years, as recently defined by the ASAS. Despite the growing recognition that early treatment is a key factor in preventing disease progression, there is currently very little evidence regarding the efficacy of advanced therapies, such as JAK inhibitors, in the early phases of axSpA.

The value of this study relies on its focus on early intervention and the new target population. Prior studies, like ESTHER and INFAST, have reported higher remission rates in patients with shorter disease duration in patients treated with TNFi. Regarding JAK inhibitors, tofacitinib has demonstrated efficacy in the treatment of AS; however, the potential for rapid and maintained disease control in early axSpA has not been researched in detail yet.

In addition, the inclusion criteria, which require signs of active inflammation on SIJ MRI and/or elevated CRP, ensure the selection of patients with objective evidence of disease activity, bringing robustness to the findings of the study. These results have the potential to impact clinical practice, supporting earlier and more targeted therapeutic strategies to prevent disease progression and improve long-term outcomes in early axSpA.

## Conclusion

This study is among the first to evaluate the efficacy and safety of the JAK inhibitor tofacitinib in patients with early active axSpA, a newly defined target population with a symptom duration of up to 2 years. While tofacitinib has demonstrated efficacy in AS, the value of this study lies in its focus on early intervention and the potential for rapid, sustained disease control in early axSpA, an area that remains underexplored.

